#### Sample size estimation

Because no previous study has examined circulating EVs in relation to MBIs and cancer, we could not use a specific effect size in estimating the sample size. Nonetheless, a recent systematic review examining the effects of Internet-based MBIs on psychological distress (anxiety and depression) found a median Cohen’s *d* value between 0.38 and 0.42 for the other primary outcome, psychological distress [14]. By using G*Power-3.1 statistical software [82] and considering repeated-measures ANOVA related to within-between interaction (group × time interaction), with an alpha significance level of 0.05 and an effect size of 0.38 (as calculated in [83]), a sample of 84 participants would allow for a power of 0.80. Additionally, previous studies showed dropout rates ranging from 12.1 to 32% for the intervention group and from 6 and 17.4% for the control group, when considering the period immediately following the intervention [23, 32, 40, 47, 49, 52, 84]. At follow-up, dropout rates were about 30.8% in the intervention group and 19.6% in the control group [52]. Considering the highest dropout rate (32%), 27 participants should be added to the estimated sample, resulting in a minimum of 111 participants to be included in the study.

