### Intervention procedures

A schematic representation of the study design from recruitment to the final follow-up time point is provided in Fig. 1. Briefly, after enrolling in the study, participants must complete the baseline survey, which consists of both biological and self-assessments. It is worthy to note that the self-reported measures are being completed via online surveys, while the biomarkers require the participants to visit the hospital for a blood sample collection. The blood samples will be preferably collected during routine clinic visits that occur in all recovered patients. After completing the baseline, participants will be randomized to one of the study conditions, internet-based MBCT or TAU. Subsequent study time points are at 4, 8, 24, and 52 weeks after baseline.

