The timing of these measures is shown in Table 4. All psychosocial measures employed at baseline (T1) are used at T3, T4, and T5. In the fourth week after the baseline (the fourth session in the case of the intervention group), self-reported measures of distress and mindfulness will be used. This intermediate point (T2) was considered as previous studies have suggested that four sessions are the minimum satisfactory intervention dose [14, 52, 84, 89]. Few measures were selected at T2 to avoid participant burden. Regarding biological samples, the plans are to collect them at T1, T3, and T4. Of note, participants will receive financial compensation for the costs they incur traveling to IPOP to participate in the blood collections.

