### Statistical methods

Screening data for errors and missing values is the first step in the data analysis plan. Missing data will be managed and avoided during the data collection by using mandatory fields in the online surveys and retrieving the data from participants when possible. Data from participants who completed fewer than 4-weekly online MBCT sessions will not be considered further, as four sessions were set as the minimum number required for participation [14].

For each group (MBCT and TAU), a summary of baseline sociodemographic and health data will be provided, including number and percentages, mean, standard deviation, median, first and third quartiles, minimum and maximum. Using the sociodemographic and health data, as well as the primary and secondary measures, comparisons will be made between groups to examine whether there are differences between groups at baseline. Similarly, differences at baseline between participants who will complete the study and those who will drop out will be examined. The presence of differences in variables may warrant the need to examine and/or adjust for their influence on outcome changes in the primary analyses. This summary also presents the within-group effect sizes (Cohen’s *d*—equation 11.10, from [135]) for each outcome across time (i.e. T1 to T2; T1 to T3; T1 to T4; T1 to T5).

The total scores of each primary and secondary measure will be used as outcomes in multiple linear mixed models (LMMs). Each model will include the interaction between group and time, while participants will be treated as a random effect. The visual inspection of Q-Q plots will be conducted to check the normal distribution of residuals. Examination of factors such as sex, type of cancer, and cancer stage will be approached by running separate models for each factor. LMM analyses can be employed using, for instance, lmer4 [136] and lmerTest [137] in R software [138].

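### The group × time mixed model does not prespecify conditioning on the pre-randomisation T1 score, so a valid test forgoes precision: about 13 to 4 points of week-8 power at assumed correlations of 0.3 to 0.8

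*Protocol article*

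**What the plan says.** Statistical methods in the protocol article puts the total score of each primary and secondary measure into a linear mixed model: "Each model will include the interaction between group and time, while participants will be treated as a random effect". No T1 covariate and no constraint on the arm means at T1 is mentioned.

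The T1 value exists before allocation. Intervention procedures states: "After completing the baseline, participants will be randomized to one of the study conditions, internet-based MBCT or TAU". It then gives the later visits: "Subsequent study time points are at 4, 8, 24, and 52 weeks after baseline". Outcome measures adds: "All psychosocial measures employed at baseline (T1) are used at T3, T4, and T5". At T2, "self-reported measures of distress and mindfulness will be used", so DASS-21 has five measurements. Blood is planned at T1, T3 and T4 only, so EV cargo has three.

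Sample size estimation uses the same kind of test, "considering repeated-measures ANOVA related to within-between interaction (group × time interaction), with an alpha significance level of 0.05", with an effect size of 0.38, 84 participants and power 0.80.

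One sentence could bring T1 into the model. Statistical methods first describes a baseline check in which, using the sociodemographic and health data "as well as the primary and secondary measures, comparisons will be made between groups". It continues: "The presence of differences in variables may warrant the need to examine and/or adjust for their influence on outcome changes in the primary analyses".

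**The concern.** A score taken before randomisation has the same expected value in both arms. A model that leaves the arm difference at T1 free ignores this: it subtracts the whole observed T1 difference from each later difference, along with the sampling noise of T1. A random intercept does not recover that loss while the T1 difference stays a free parameter.

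Two things are at stake. First, power, in a trial whose Discussion already concedes that the EV outcome may be underpowered. Second, sensitivity to chance imbalance. Given an observed T1 difference of 0.2 SD, the raw-change estimate is shifted by (1−ρ) × 0.2, which is 0.10 SD at ρ = 0.5, or 0.10/0.38 = 26% of the assumed effect. Over repeated randomisations this averages to zero, but it affects the one trial that is run.

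**Working it through.** **Inputs.** From the protocol: N = 84 with 1:1 allocation, so n = 42 per arm; effect size 0.38; alpha 0.05, taken as two-sided for single contrasts; five measurements for DASS-21 and three for EV cargo. Assumed, because not given: the correlation ρ between visits (0.3 to 0.8 shown), unit variance, compound symmetry as a random intercept implies, no dropout, and 0.38 read as the standardised arm difference at a visit.

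**The plan's own figure.** Take f = 0.38/2 = 0.19, five measurements, and the G*Power option in which the noncentrality is f²·N·(m−1). Then λ = 0.0361 × 84 × 4 = 12.13 on 4 and 82 × 4 = 328 df, and power is 0.801. The stated 84 is reproduced for the interaction test that the plan intends to use.

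**What the interaction estimates.** Let D_t be the MBCT minus TAU difference in means at visit t. In simulated complete data, the four interaction coefficients of a random-intercept model with categorical time equalled the differences in raw mean change to all printed digits. So:

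- Planned contrast: D_3 − D_1, with variance (2/n) × 2(1−ρ).
- Conditioned on T1: D_3 − ρD_1, with variance (2/n) × (1−ρ²).
- Ratio, conditioned to planned: (1−ρ²)/(2(1−ρ)) = (1+ρ)/2, which is below 1 for every ρ < 1.

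**Week-8 contrast, example at ρ = 0.5.** Planned: variance 2/42 × 1 = 0.0476, SE 0.218, noncentrality 0.38/0.218 = 1.74. Conditioned: variance 2/42 × 0.75 = 0.0357, SE 0.189, noncentrality 0.38/0.189 = 2.01. Power comes from the noncentral t on 82 df:

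| ρ | variance ratio | planned | conditioned | loss (points) |
|---|---|---|---|---|
| 0.3 | 0.65 | 0.31 | 0.44 | 13 |
| 0.5 | 0.75 | 0.41 | 0.51 | 10 |
| 0.6 | 0.80 | 0.49 | 0.58 | 9 |
| 0.7 | 0.85 | 0.60 | 0.67 | 7 |
| 0.8 | 0.90 | 0.78 | 0.82 | 4 |

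**Omnibus test.** For q post-baseline visits and a constant d, with (n/2)d² = 21 × 0.1444 = 3.032:

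- Planned: λ = 3.032 × [q/(q+1)]/(1−ρ).
- Conditioned: λ = 3.032 × q/[(1−ρ)(1+qρ)].

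At ρ = 0.5 and q = 4 these are 4.85 and 8.09. The fading pattern below has differences of 0.19, 0.38, 0.28 and 0.19 at T2 to T5. Degrees of freedom are 4 and 328 for five measurements, and 2 and 82 × 2 = 164 for three.

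| Test | ρ 0.5 | ρ 0.7 | ρ 0.8 |
|---|---|---|---|
| Five visits, sustained d = 0.38 | 0.38 vs 0.60 | 0.60 vs 0.74 | 0.80 vs 0.87 |
| Five visits, fading effect | 0.26 vs 0.38 | 0.43 vs 0.51 | 0.61 vs 0.68 |
| Three visits (EV cargo), illustrative d = 0.38 | 0.41 vs 0.58 | 0.63 vs 0.73 | 0.81 vs 0.87 |

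The losses, from unrounded values, are about 22, 14 and 7 points (sustained), 11, 8 and 6 (fading), and 17, 10 and 5 (EV cargo). At ρ = 0.8 with a sustained effect, the planned λ is 3.032 × 0.8/0.2 = 12.13, the same as in the plan's own sizing.

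**Does the analysis set matter?** Statistical methods also drops MBCT participants who attended fewer than four sessions, a rule that can remove people from one arm only. Suppose those removed have higher stable distress and there is no treatment effect. A gap g then appears at T1 and again at follow-up. Raw change gives g − g = 0. The T1-conditioned estimate gives g − ρg = (1−ρ)g. Simulation at ρ = 0.5 with 60 per arm and 27 to 35% of the MBCT arm excluded in this way (assumed; the protocol cites intervention-arm dropout of up to 32%) gave a T1 gap of 0.12 to 0.22 SD. The T1-conditioned bias was 0.06 to 0.11 SD in favour of MBCT, and raw change stayed within 0.005 SD of zero. Other selection patterns would give other results.

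**The case against.** The case for leaving the plan alone has real content.

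- **The reading is inferred.** The article does not list the time levels, say that time is categorical, or state a group main effect, and a condensed article may leave such detail elsewhere. This stands as a caveat. The interaction is nevertheless stated as the analysis, the sizing uses it, and within-group effects are reported from T1 to each later visit, so T1 as a level of time is the natural reading.
- **The baseline-adjustment sentence can cure it.** A reader might infer that the loss remains whatever covariates are added. It does not: with T1 × time added to the random-intercept model, the interaction coefficients matched the T1-conditioned estimates to six decimals. The sentence covers the primary measures. What remains is that adjustment depends on an observed difference and its form is not fixed.
- **The test is sound.** A reader might infer bias or an underpowered design from this choice. Neither follows. Leaving aside the exclusion rule, raw change is unbiased under randomisation, and 84 was computed for that same interaction. Power values below 0.80 in the tables reflect the assumed ρ and effect pattern; only the gap between the two models bears on this point.
- **No single figure for the loss is supported.** A flat 10 to 20 points would need a correlation that the documents do not give. The five-visit results also do not carry over to EV cargo.
- **Conditioning is not free of risk.** Equal T1 means hold by design only in the randomised set. This stands, and it limits the fix.

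**Conclusion.** The point holds as one of efficiency. The plan does not commit to conditioning on T1, and as naturally read it tests a difference in raw change. That is less precise than a T1-conditioned analysis at any correlation below 1.

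Under the stated assumptions the week-8 loss runs from 13 points (ρ = 0.3) to 4 points (ρ = 0.8). Omnibus losses for ρ of 0.5 to 0.8 are 22 to 7 points with a sustained effect, 11 to 6 with a fading one, and 17 to 5 for EV cargo at an illustrative d. The direction does not depend on ρ; the size does. The change is worth making because the T1 data are already collected, but the planned analysis is not an error.

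**What to change.** In Statistical methods, replace the model sentence with wording such as: *For each outcome measured at T1, the post-baseline visits are the responses. The model includes group, visit, group × visit, T1 and T1 × visit, with participant as a random effect. The treatment effect is the adjusted between-arm difference at each post-baseline visit. T1 is included whatever baseline difference is observed. Participants are analysed as randomised.*

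A constrained longitudinal model with equal arm means at T1 is an equivalent option in the full randomised set. Visits follow each outcome's own schedule: T2 to T5 for DASS-21, T3 and T4 for EV cargo and the other blood markers.

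The cost is one sentence and one line of model code, with no new data or visits. The condition is the analysis set: if MBCT participants with fewer than four sessions are still left out of the primary analysis, conditioning on T1 can introduce bias that raw change would avoid in the scenario above. The two changes should therefore be made together.

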#### Experimental group

The MBCT programme [85] is a manualized group-based training programme that combines aspects of cognitive-behavioural therapy and aspects of the MBSR programme [86]. It was originally developed to reduce the risk of relapse and recurrence associated with major depression, but has also been used for other clinical conditions (e.g. cancer; chronic pain; vascular disease) with satisfactory results (see [87] for an overview). We selected this programme as it has been used in cancer patients with moderate to high levels of distress and has also shown promising results in an online setting [31, 41, 42, 84, 88, 89].

During the programme, participants learn mindfulness skills to bring attention to the present moment and foster increasing awareness of body sensations, thoughts, and feelings. This includes recognizing and accepting negative and unwanted thoughts, as well as the transitory quality of feelings. The idea is to allow the mind to move from automatic and spiralling patterns to a more conscious processing of mental and physical activities [90]. Overall, the awareness of the usual patterns of the self shall help to manage and accept unwanted thoughts and feelings.

The online MBCT programme that is being used in this study will be as close as possible to a face-to-face version. It consists of eight weekly 2-h sessions in a group setting (usually 12 participants), follow-up sessions, and an online retreat that addresses meditation skills and is led by a mindfulness facilitator [15, 85]. The general structure of the MBCT programme is as follows: the first four sessions are devoted to promoting basic mindfulness skills and psychoeducation regarding unhelpful thoughts; the last four sessions promote an accepting attitude towards unhelpful thoughts and feelings. Each session usually begins with mindfulness and meditation exercises, followed by group discussion, a review of homework activities, and the introduction to new exercises. A summary of the programme can be found in Table 2.

**Table 2 Tab2:** Overview of the activities planned for the 8-week online MBCT group

Sessions (general theme)	Synchronous class activities	Asynchronous homework activities

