Session 7 (acknowledge warning signs and plan preventive strategies to tackle the occurrence of unpleasant events)	Mindfulness meditation exercises: sitting meditation; 3-min breathing space; mindful walking Investigate associations between activity and mood Have a list of pleasant activities and how to schedule them Continue to work on the response plan in pairs and then extend it to the group	From the practiced exercises, generate a plan of practice to be incorporated into daily routines 3-min breathing space 3-min breathing after acknowledging the appearance of unhelpful feelings and thoughts Continue to work on the response plan
Session 8 (maintain mindfulness-related practices on a regular basis)	Mindfulness mediation exercises: body scan and concluding meditation Continue to work on the response plan and detection of early warning signs Review and personal reflections regarding the programme (feedback questionnaire) Discussion on how to keep daily practices	Keep on practicing

*Note*. *MBCT* mindfulness-based cognitive therapy

Synchronous sessions and interactions will be conducted via videoconference with the facilitator and other group members (maximum of 12 participants). In addition to the online sessions, participants will be encouraged to complete daily asynchronous homework assignments using support materials created and provided by the programme. For this purpose, participants will be provided with audio-guided exercises shared via an online file hosting service and mp3 players. Participants will be expected to complete daily practices of 10–40 min six times per week. Home practice will be monitored weekly using online surveys. A 4-h online retreat is proposed after the fifth week of intervention, and 4 monthly booster and consolidation sessions of 2 h are scheduled after the synchronous sessions.

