#### Treatment as usual (TAU)

Participants in TAU group will follow the routine intervention protocol established by the hospital for needs assessment, referral, follow-up, and management of individuals with significant distress difficulties. Participants will be monitored for recurrence of cancer or other health problems, changes related with pharmacological and non-pharmacological interventions, and the occurrence of other major life events.

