Motivation during the programme is supported and intensified in synchronous group sessions led by instructors, as interpersonal interactions and peer group support have been identified as relevant aspects in online MBIs [21, 31, 34, 53]. Previous studies indicated that participants need to receive reminders about daily training [44]. MBIs that include reminders have been shown to be more likely to have greater effects on outcome measures than MBIs without reminders [28]. Reminders may also lead to better completion rates [95]. However, there is a lack of evidence in the literature about how often these reminders should be given to promote engagement and not an opposite effect (see [14] for a discussion). In this study, we will adopt some of the strategies reported in previous studies, including twice-weekly email reminders [47], reinforced reminders during the synchronous sessions [96], and additional reminders to unresponsive participants [22, 23]. In addition to these interventions, four booster sessions will be implemented to avoid the feelings of disengagement that participants may experience after weekly sessions [97].

The following feasibility measures are considered: recruitment rates (e.g. the proportion of individuals who responded with interest to our invitation; the proportion of individuals who agreed to participate in the study, regardless of eligibility; the proportion of individuals who completed the first assessment point—T1—and began the intervention); adherence to practice (e.g. number of attended sessions; the number of homework assignments completed per week; the average time spent practicing at home each day); programme completion and dropout rates; and programme satisfaction.

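### The stated mixed model and sample size make no allowance for MBCT classes, so the group-by-time standard error is too small if outcomes within a class are correlated

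*Protocol article*

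**What the plan says.** The Statistical methods section sets linear mixed models for every primary and secondary score: "Each model will include the interaction between group and time, while participants will be treated as a random effect". It names no term for class or instructor, and it does not mention random slopes, residual covariance or degrees of freedom.

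The Experimental group section describes MBCT as "eight weekly 2-h sessions in a group setting (usually 12 participants" and caps the videoconference groups: "other group members (maximum of 12 participants". The control arm is different: "Participants in TAU group will follow the routine intervention protocol established by the hospital", with no classes described.

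Sample size estimation uses a repeated-measures ANOVA for the group × time interaction (alpha 0.05, effect size 0.38, power 0.80). It arrives at 84 participants, adds 27 for 32% dropout, and reaches 111. Clustering is not mentioned.

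On timing, Intervention procedures says "Subsequent study time points are at 4, 8, 24, and 52 weeks after baseline". For blood samples, which carry the extracellular vesicle (EV) primary outcome, Outcome measures says "Regarding biological samples, the plans are to collect them at T1, T3, and T4", that is, weeks 0, 8 and 24.

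**The concern.** People taught in the same class share sessions, peers and teaching, so their outcomes after the programme starts may resemble one another. A participant effect absorbs correlation between visits of one person; it does nothing for correlation between people. The model as written therefore treats some 55 MBCT participants as 55 independent units, although part of the arm comparison may rest on about five classes. The sample size makes the same assumption.

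The article states the random-effects structure, so the point concerns a stated choice and not an omitted detail. At stake are the confidence interval and p-value for the group-by-time effect on both primary outcomes, and the 80% power claim.

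A lesser question is whether a participant effect alone suits visits spaced from 4 to 52 weeks.

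**Working it through.** **Inputs from the article.** 1:1 allocation; classes of at most 12; alpha 0.05; effect size 0.38; N = 84 before and 111 after dropout; visits as above. With 111 randomized, the MBCT arm has 55 or 56 people, and 56/12 = 4.7, so about five classes.

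**Assumptions.** The documents give no class ICC and no correlations between visits. I take ICCs from 0 to 0.10. The ICC meant is that of the change from baseline being compared.

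**1. The plan's own figure.** Noncentral F with noncentrality f²N, f = 0.38, two groups and five measurements (df 4 and 4 × 82 = 328) gives power 0.801 at N = 84. The article does not state the number of measurements or the software option; these settings reproduce 84. And 84 × 1.32 = 110.9, hence 111. I take f = 0.38 as given here.

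**2. Clustering in one arm.** With equal arms and class size m, the true variance of the arm difference relative to the naive variance is

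v = {[1 + (m − 1) × ICC] + 1} / 2.

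The two-sided type I error is 2 × [1 − Φ(1.96/√v)]. For m = 12 and ICC = 0.05: v = (1.55 + 1)/2 = 1.275, √v = 1.13, 1.96/1.13 = 1.74, type I error 0.083.

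For power, I divide the plan's noncentrality by v: at ICC 0.05 it is 0.38² × 84/1.275 = 9.5 instead of 12.1. This ignores the degrees of freedom lost to having few classes, so it is slightly favourable. For dropout, 12 × 0.68 = 8.2, so the m = 8 column shows classes shrunk by the plan's 32%.

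| Assumed ICC | v (m = 12) | True SE / naive SE | Type I, m = 12 | Type I, m = 8 | Power at N = 84 | N for 80%, before dropout |
|---|---|---|---|---|---|---|
| 0 | 1 | 1 | 0.050 | 0.050 | 0.801 | 84 |
| 0.01 | 1.055 | 1.03 | 0.056 | 0.054 | 0.776 | 90 |
| 0.02 | 1.11 | 1.05 | 0.063 | 0.058 | 0.752 | 94 |
| 0.05 | 1.275 | 1.13 | 0.083 | 0.071 | 0.684 | 108 |
| 0.10 | 1.55 | 1.25 | 0.115 | 0.092 | 0.587 | 130 |

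The last two columns use m = 12.

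**3. Simulation.** The random-intercept analysis with balanced complete data (42 per arm, 4,000 runs, equal correlation between visits) rejected a true null group × time effect in 0.058, 0.077 and 0.096 of runs at ICC 0.02, 0.05 and 0.10. An analysis of a single change score by class means with Satterthwaite degrees of freedom (four or five classes, 20,000 runs) gave 0.049 to 0.059 over ICC 0 to 0.10. The naive test of that score gave 0.061 to 0.110 over ICC 0.02 to 0.10.

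**4. Where a class effect must enter.** Write an MBCT participant's outcome at visit t as mean + u + other terms, with u a class effect that is constant over visits. The change from baseline is then (… + u) − (… + u), and u cancels. A plain class intercept would leave the group-by-time standard error uncorrected. Baseline also precedes randomization, so teaching cannot have acted on it. The class effect has to act on the post-baseline visits.

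**5. Visit spacing, without clustering.** With equal variances and complete data, a random-intercept model takes the variance of a person's change as 2σ²(1 − ρ̄), where ρ̄ is the average correlation over all pairs of visits. The true variance is 2σ²(1 − ρ₁ⱼ). The standard error is too large where ρ₁ⱼ exceeds ρ̄ (early visits) and too small where it falls below (late visits). Simulated under an assumed correlation that decays with time:

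- Self-report: rejection 0.006, 0.018, 0.057 and 0.102 for baseline to weeks 4, 8, 24 and 52; overall interaction test 0.068. With a modest random slope instead: overall 0.046, week 52 0.069.
- Blood samples: 0.024 at week 8, 0.080 at week 24, overall 0.056.

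**The case against.** The strongest reply is that the harm is conditional. No ICC is given, and at ICC 0 nothing is wrong; at 0.01 to 0.02 the error rate is only about 6%. If one person teaches every class, the instructor adds no variation between classes. Dropout, and the exclusion of those attending fewer than four sessions, would shrink the classes. The number of classes is inferred, since 111 is a minimum. All of this stands, and it is why the sizes above are a range under assumptions.

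A reader might infer that the Adherence and feasibility section already calls peers an active ingredient. It does not: it says that "interpersonal interactions and peer group support have been identified as relevant aspects in online MBIs", in a passage about motivation. That makes some within-class correlation plausible but does not establish it.

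A reader might also infer that visits running from 4 to 52 weeks inflate false positives generally. Step 5 shows otherwise: early contrasts become conservative, the 52-week contrast anti-conservative, and the overall test stays near nominal. The 52-week contrast does not exist for the EV outcome. Moreover, the article does not say that the participant effect is an intercept alone, and a condensed article may leave residual covariance to a fuller plan. The spacing point is therefore secondary and conditional.

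The reply does not remove the main point. The article names the random effect, describes classes in one arm, and connects the two neither in the model nor in the sample size.

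**Conclusion.** The point holds in conditional form. The stated model and sample size assume independent participants, while one arm is taught in classes of up to 12. For any class ICC above 0 the group-by-time standard error is too small. With full classes and ICCs of 0.02 to 0.10, it is understated by a factor of 1.05 to 1.25, type I error is about 6% to 12%, and power at N = 84 is about 75% to 59%. With classes of 8 the type I error is about 6% to 9%. These figures rest on assumed ICCs, and the power figures also on the settings that reproduce 84.

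The documents do not support saying that the false-positive rate is inflated as a matter of fact, or that visit spacing inflates it. The matter should be settled before analysis; it does not undermine the trial.

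**What to change.** Record each MBCT participant's class. In the MBCT arm only, add a class-level random effect on the post-baseline visits (class by visit, with TAU participants as singletons), using Satterthwaite or Kenward-Roger degrees of freedom. Report the class ICC. In the sample size section, state that 80% power with 84 participants assumes a class ICC of zero, and show the power under a few non-zero values.

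As a secondary change, specify an unstructured within-person covariance over the fixed visits in place of a random intercept alone.

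The cost is mainly wording and a different model call. The R packages the article offers as an example do not directly fit an unstructured residual covariance, so other software may be needed. Intervals will be wider. With about five classes the class variance will be imprecisely estimated and may come out at zero, so the plan should say beforehand what is then reported. Holding 80% power at ICC 0.05 would need 108 participants before dropout instead of 84; if recruitment cannot grow, the lower power should be acknowledged.
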